**Methods:**

A prospective, multicenter, and observational study will be conducted in all 20 Brazilian NICUs using the *PBSF Guidelines* as standard-of-care. All infants treated accordingly to the guidelines during Dec 2021 to Nov 2024 will be eligible. Ethical approval was obtained from participating centers. The primary objective is to describe adherence to the *PBSF Guidelines* and clinical outcomes, by center and over a 3-year period. Adherence will be measured by quantification of neuromonitoring, neuroimaging exams, sub-specialties consultation, and clinical case discussions and videoconference meetings. Clinical outcomes of interest are detection of seizures during hospitalization, use of anticonvulsants, inotropes, and fluid resuscitation, death before hospital discharge, length of hospital stay, and referral of patients to specialized follow-up.

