### Eligibility criteria

In this study, the NICUs eligibility criteria are to have adopted the PBSF guidelines and agree to participate in the study (S2 Appendix). The characteristics of each NICU will be recorded and described. In those NICUs, all infants admitted from birth up to 3 months of age, and submitted to the *PBSF Guidelines* during the study period will be eligible. Indications for the use of the *PBSF Guidelines* are provided on Box 1. The *PBSF Guidelines* is the standard-of-care for high-risk newborns at all these hospitals. Patients with genetic syndromes or malformation incompatible with life will not be included. Details on the *PBSF Guidelines* are provided in (S3 Appendix). Briefly, it includes provision of equipment and resources, connection between the associated NICU and the remote monitoring center called the *Central of Surveillance and Intelligence (CSI)*, training and teaching of all health care professionals of each NICU, and customized multiparametric recordings of biological signals from each patient. At the CSI, a team is available 24 hours a day all year around, allowing for case discussions and simplified reports with brain monitoring information at the patient monitor’s display every 6 hours.

Box 1. Indications for use of the *PBSF Guidelines* in the participating centers.IndicationsExtreme prematurityPeri-intraventricular HemorrhageHypoxic-ischemic encephalopathy (mild, moderate, or severe)Congenital heart diseaseNeonatal strokeCongenital infectionsNosocomial infectionsInborn errors of metabolismSevere hemodynamic/ventilatory instabilitySeizuresBrain malformationsCentral nervous system infectionExtracorporeal membrane oxygenationPBSF, protecting brains and saving futures.

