### Variables

Population demographics: gender, type of delivery, gestational age at birth, gestational age ≤ 32 weeks and < 37 weeks, Apgar score at 1 min, 5 min and 10 min, birth weight, current weight, inborn or out born, use of antenatal steroids and magnesium sulfate. Primary diagnosis: seizure, mild HIE, moderate or severe HIE/cooling, neurologic abnormalities or congenital central nervous system (CNS) anomalies, grade III or IV intraventricular hemorrhage (IVH) or hydrocephalus, periventricular leukomalacia, meningitis, neural tube defects, stroke, cyanotic congenital heart defect (CHD), prematurity, gestational age ≤ 32 weeks, meconium aspiration syndrome, cardiorespiratory instability (anemia, shock and respiratory alkalosis/acidosis), necrotizing enterocolitis, metabolic disease, extracorporeal membrane oxygenation (ECMO)/pre-ECMO. For descriptive analysis patients will be divided into two groups accordingly to their primary diagnosis: neurological or clinical. A minimal anonymized data set necessary to replicate future study findings is provided as (S4 Appendix).

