### Data collection and management

Patient demographics, diagnosis and clinical outcomes will be extracted from the medical charts of each patient and entered in the PBSF database. The *adherence to the PBSF Guidelines* will be measured with the data collected by the *CSI* center. Details of these recordings are provided on S3 Appendix.

A flow chart of all eligible and enrolled patients will be produced, and the total number of patients will be reported, overall and per center.

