Brazil allows several opportunities for telemedicine implementation, expanding the actions of healthcare professionals and integrating healthcare services [86]. We developed the *PBSF Guidelines* with a surveillance and intelligence center to support clinical decisions across the country. Telemedicine has been used by our group in the past few years to promote educational training and remote neuromonitoring but its impact on clinical outcomes needs to be formally evaluated. Thus, results of this 3 years prospective, multicenter, and observational study will help to determine the incidence of neonatal problems associated with brain injury and disabilities, the incidence of clinical and subclinical seizures, detection of brain hemodynamic/oxygenation instability and associated interventions. The study will be limited to the 20 NICUs using the *PBSF Guidelines* and variability in clinical practices, experience of health care providers and staffing of the units, will be analyzed as it may affect some of the outcomes. Enrollment of such large number of patients will require a strong coordination between the central unit and all 20 centers, which has already been established by the CSI. Practical or operational issues will be to assure that all eligible patients are identified in a daily basis and approached for consent. Data collection requires careful training of data extractors and timely and precise data entry. A computerized and safe double-checking system has been developed. Biological signals will be continuously collected and stored at the CSI and multimodal signal analysis has been developed. Although low, there are costs for the implementation and use of the *PBSF Guidelines*. Thus, an adjusted analysis based on the profile of the units will be performed as costs might represent a limitation on the generalizability of the study findings. A future cost/benefit analysis is under planning.

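### The Discussion promises incidence of brain-injury problems and of clinical and subclinical seizures, but those conditions are reasons for entry and the only listed seizure outcome is an EEG count

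*Protocol article*

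**What the plan says.** Near its end, the Discussion states that the results will "help to determine the incidence of neonatal problems associated with brain injury and disabilities, the incidence of clinical and subclinical seizures".

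The cohort is defined under Eligibility criteria: "all infants admitted from birth up to 3 months of age, and submitted to the *PBSF Guidelines* during the study period will be eligible". The abstract says the same: "All infants treated accordingly to the guidelines during Dec 2021 to Nov 2024 will be eligible". Box 1 lists the indications for using the Guidelines. They include seizures, peri-intraventricular hemorrhage, hypoxic-ischemic encephalopathy (HIE), neonatal stroke, brain malformations and central nervous system infection. Ethics approval and consent to participate adds that written consent is obtained before inclusion.

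The Variables section records one relevant baseline item, beginning "Primary diagnosis: seizure, mild HIE, moderate or severe HIE/cooling". Seizure is its own category there, not divided into clinical and subclinical. For description, patients are grouped by primary diagnosis as neurological or clinical.

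In Box 2 the only seizure outcome is a count of EEG seizures during the hospital stay. It is one of the primary outcomes. Under Outcomes and Statistical methods, results are described overall and by center, compared across years 1, 2 and 3 within and between centers, and compared between the neurological and clinical groups. The Introduction hypothesizes that adherence will rise over time and that this will go with better clinical outcomes.

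**The concern.** A frequency measured in infants who were partly selected because they already had the condition reproduces the entry rule to some degree. For seizures this concerns more than one sentence of Discussion, because EEG seizures are a primary outcome to be compared between years and between centers. If a center widens or narrows the group it places on the Guidelines, the seizure figure shifts with no change in care or in underlying risk. A reader could then take a change in indication mix for an effect of adherence, which is what the hypothesis in the Introduction invites.

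The second part is a mismatch between a promised result and the listed outcomes. Separating clinical from subclinical seizures requires each EEG seizure to be classed by whether a clinical sign accompanied it. Clinical events without an EEG correlate would also have to be counted if those are meant. Box 2 and Box 3 list neither. The distinction matters to the protocol's own argument, since the Discussion says that most neonatal seizures are subclinical and that clinical diagnosis is unreliable.

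**Working it through.** **Step 1. Entry criterion against outcome.** Box 1 has seizures as an indication. Box 2 has EEG seizures as an outcome. Hemorrhage, HIE and stroke are likewise Box 1 indications and also belong to the brain-injury problems whose incidence the Discussion mentions. For these conditions, selection into the cohort and the quantity to be reported overlap.

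**Step 2. Does the planned analysis separate the two?** Three features come close.
- The neurological/clinical grouping places infants entered for seizures together with infants entered for HIE, stroke or hemorrhage, so it does not isolate them.
- Statistical methods says overall analyses will allow for site differences or within-site correlation. That does not address a change in indication mix over time within a site.
- The adjustment in Outcomes is for the unit's funding profile, which is a different factor.

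The recorded primary diagnosis would allow the separation, but no described analysis uses it at that level.

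**Step 3. Clinical/subclinical split.** The Discussion promises both. Variables has an undivided seizure category, Box 2 has EEG seizures only, and Box 3 has no seizure item. The split has no listed outcome.

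**Step 4. Illustration of size.** The protocol gives no seizure frequency and no indication shares, so there is no figure of its own to reproduce and every input below is assumed. Take the outcome as the proportion of infants with at least one EEG seizure. Let *s* be the share of enrolled infants who enter because of seizures, *c* the proportion of these with a seizure on EEG, and *r* the proportion with a seizure on EEG among all others. Then

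cohort frequency = *c* × *s* + *r* × (1 − *s*).

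With *r* = 0.10 held fixed:

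| *s* | *c* = 1 | *c* = 0.5 |
|---|---|---|
| 0.10 | 0.10 + 0.09 = 19% | 0.05 + 0.09 = 14% |
| 0.20 | 0.20 + 0.08 = 28% | 0.10 + 0.08 = 18% |
| 0.30 | 0.30 + 0.07 = 37% | 0.15 + 0.07 = 22% |

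From the first row to the last, the figure rises by a factor of 37/19 = 1.95 when every seizure-entry infant has an EEG seizure, and by 22/14 = 1.57 when half do. In both columns the risk in the remaining infants is constant at 10%. The table shows the mechanism; it does not estimate what will happen in this study.

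**The case against.** The strongest reply is that this is one sentence of Discussion prose, worded as helping to determine. The abstract objective and the aim in the Introduction are adherence and clinical outcomes, and neither mentions incidence. No listed outcome is called an incidence and no planned test estimates one. This stands, and it limits the weight of the wording issue. It does not remove the selection problem from the EEG-seizure comparison, which is a listed primary outcome.

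A reader might infer that the protocol claims a population incidence and fails because births and NICU admissions are not counted. The documents do not support that. The sentence after the incidence claim confines the study to the 20 participating NICUs. A cohort denominator is promised: "A flow chart of all eligible and enrolled patients will be produced, and the total number of patients will be reported, overall and per center". New events in a defined, followed cohort are ordinarily called incidence. NICU characteristics are also to be recorded, without a list in the article.

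A reader might also infer that no field for clinical signs exists. That cannot be confirmed: "A minimal anonymized data set necessary to replicate future study findings is provided as (S4 Appendix"), and that appendix, the recording details in S3 Appendix and the original protocol in S7 File are not shown. What can be said is that the article's listed outcomes contain no such classification.

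A third inference would be that "detection of brain hemodynamic/oxygenation instability and associated interventions" is equally unsupported. That is too strong. The Discussion says biological signals are stored at the central monitoring unit and that a multimodal signal analysis has been developed, and Box 2 lists inotropes and fluid resuscitation. A derived oxygenation endpoint is detail that an article may leave to the full protocol.

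Finally, the recorded primary diagnosis makes stratification possible. That is correct, and it is why the remedy is cheap. But a variable that could be used for the split is not yet a plan to use it.

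**Conclusion.** The point holds in a limited form. The cohort is selected on indications that include the conditions whose incidence is announced, so the measured frequency and its comparison across years and centers partly reflect who is placed on the Guidelines. The listed outcomes do not support a clinical/subclinical split. These two statements rest only on Box 1, Box 2, Box 3, Variables, Statistical methods and the Discussion.

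The size in this study is unknown. The range in the working (19% to 37%, or 14% to 22%) depends on an assumed 10% in the remaining infants, assumed entry shares of 10% to 30%, and an assumed EEG confirmation of all or half of seizure-entry infants. It should be read as illustration only. No stated objective, sample size or planned test has to change. What is needed is a stratified report of a primary outcome and a narrower claim.

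**What to change.** 1. In the Discussion, replace the incidence wording with frequency among consented infants managed under the PBSF Guidelines.
2. Report EEG seizures separately for infants whose primary diagnosis at entry is seizure and for all other infants, and carry this split into the year and center comparisons. Do the same for the other Box 1 conditions reported as results. State that the primary diagnosis used for the split is the one held at entry, so that seizures first found by monitoring are not moved into the seizure-entry group. Where Box 1 and Variables word a condition differently (hemorrhage has no grade in Box 1 and is grade III or IV in Variables), state how they map.
3. Either list a classification of EEG seizures by accompanying clinical sign as an outcome, or drop the clinical/subclinical claim. If the unshown data set already holds that field, it only has to be named as an outcome.

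Items 1 and 2 need wording and extra table rows, using a variable already collected. Item 3 needs at most one form field. The price is a narrower stated conclusion and, within strata, smaller numbers per center and year.

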## Abbreviations

aEEG: Amplitude Integrated Electroencephalography
CBF: Cerebral Blood Flow
CHD: Congenital Heart Defect
cMRI: Cranial Magnetic Resonance Imaging
CNS: Central Nervous System
CSI: Central of Surveillance and Intelligence
cUS: Cranial Ultrasonography
ECMO: Extracorporeal Membrane Oxygenation
EEG: Electroencephalography
HIE: Hypoxic-Ischemic Encephalopathy
HR: Heart Rate
hsPDA: Hemodynamically Significant Patent Ductus Arteriosus
ICU: Intensive Care Units
IVH: Intraventricular Hemorrhage
MLPT: Moderate and Late Preterm Infants
NIBP: Non-invasive Blood Pressure
NICU: Neonatal Intensive Care Unit
NIRS: Near Infrared Spectroscopy
PBSF: Protecting Brains & Saving Futures
pCO_2_: Partial Pressure of Carbon Dioxide
PGE: Prostaglandin
RCT: Randomized Controlled Trials
rScO_2_: Cerebral Tissue Oxygenation
rSO_2_: Cerebral and Somatic Tissue Oxygenation
rSrO_2_: Renal Tissue Oxygenation
SpO_2_: Pulse Oximetry
SWC: Sleep-Wake Cycle
TH: Therapeutic Hypothermia
WHO: World Health Organization
WMI: White Matter Injury
